### Recruitment, Randomization, and Procedures

Successful recruitment and retention strategies previously established by our team will guide this study [27,34,52-54]. A stratified sampling strategy followed by randomization will be used. This sample will mirror Florida demographics and aim to recruit participants in the following percentages: female (51%), male (49%), Black (16%), Hispanic (26.4%), White (77%), and other races (7%). At both clinical sites, a research assistant will screen all new patients for eligibility using their respective electronic medical record systems. Eligible patients will be approached by the research assistant at their first chemotherapy appointment and asked to participate. In our pilot study, this timing acted as a distraction for patients while they waited for chemotherapy to start and did not interfere with treatment, nursing care, or education. In addition, prior to treatment, all patients have received standard written education regarding treatment effects and will expect CINV as a possible effect of treatment; therefore, being approached about the study is not expected to elicit anxiety. Informed consent will be obtained in a private area of the clinic open to the research assistant, and a copy of the consent form will be given to the participant.

Once informed consent is obtained, baseline measures will be completed, and participants will be randomized (IG and ACG) to either group by choosing an envelope with a group assignment. If they are randomized to the IG, the intervention will begin immediately. Regardless, participants in each group will receive standard care (1) on admission to the cancer center (receipt of standard written educational materials that patients are instructed to bring to each appointment), (2) at a treatment planning visit in the clinic (receipt of specific handouts regarding treatment and potential side effects, and (3) at time of treatment (verbal review of chemotherapy and symptom handouts by treatment center or chemotherapy nurses). Retention of all participants will be enhanced with (1) weekly follow-up telephone calls and (2) ACG offered MAH at the end of the study.

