#### Part 1: The MAH Serious Game

The game will be administered and supervised by the research assistant. Participants will play the game on an iPad at the outpatient treatment center prior to their first chemotherapy treatment. Headphones can be used to ensure privacy and limit distraction. During the game, players make decisions for the avatar based on common CINV management practices (eg, taking medication, dietary strategies, and staying hydrated; Textbox 1), which cause the avatar to become nauseated or be nausea-free.

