### Data Collection

Once enrolled in the study (T_1_—baseline), research assistants will electronically record information about the participants’ diagnosis and treatment plan collected from medical records. Participants in both groups will complete baseline questionnaires electronically on an iPad given to them by the research assistant. The research assistant will demonstrate how to complete the electronic questionnaire and assist with any questions or issues that may occur during data collection. The research assistant will also meet with participants at subsequent treatment cycles (T_2_-T_6_) to have them fill out the electronic questionnaires on the iPad. Assistance will be given as needed.

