### Data Management and Integrity

All data will be stored using REDCap (Research Electronic Data Capture; Vanderbilt University) [60], a secure web application database, which will be accessed by a secure web connection with authentication and data logging. Due to the multisite feature of this study, 2 separate REDCap systems will be set up on the University of Miami and University of Central Florida servers separately, but they will share the same structure so that the data could be communicated and analyzed in a consistent way. For surveys that will be filled out by participants electronically, a secured and unique link will be sent via email or text so that the data can be captured accurately. A unique identifier associated with each participant will also be incorporated into the surveys so that the survey responses could be easily identified and rechecked by research staff. Research assistants will also use this identifier when they enter data from the electronic medical record and from their checklists. For any paper and pen surveys, the project director or research assistants will review all data for completeness and appropriate entries before it is entered into the study database.

At the beginning of the data entry process, a minimum of 1 in every 10 participant records will be checked against the original record for data errors. Records for review will be randomly chosen by the data manager. As the study progresses, the frequency of monitoring will be based on the results of the previous data review. If the error rate is unacceptable, then the monitoring will increase until the error rate is acceptable (less than 5% of all data). In consultation with the principal investigator (VL), the data manager will develop reports that will help in the coordination and management of the project and also allow project staff to monitor the quality of the data and the progress of the study. The data files will be backed up daily during the data entry process and once a month when data collection is complete by the data manager. All data files will be housed on the university servers, which are backed up every 24 hours, and copies will be stored off-site for additional security. Access to the database will be password-protected and limited to the investigators, research personnel, project director, and data manager. Furthermore, the user rights will be assigned appropriately by the project manager or data manager to ensure data security and privacy.

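### Allocation by a participant's free choice of envelope, at the visit where the research assistant role enrols and delivers the game, is not shown to be concealed or auditable, and site enters neither the described allocation nor the models

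*Protocol article*

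**What the plan says.** All references are to the protocol article.

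- **Mechanism.** Recruitment, Randomization, and Procedures: "Once informed consent is obtained, baseline measures will be completed", and then "participants will be randomized (IG and ACG) to either group by choosing an envelope with a group assignment". For those drawn to the intervention group, the game starts straight away.
- **Who is present.** In the same section, "a research assistant will screen all new patients for eligibility using their respective electronic medical record systems" and "Eligible patients will be approached by the research assistant at their first chemotherapy appointment and asked to participate". Part 1: The MAH Serious Game adds "The game will be administered and supervised by the research assistant". Data Collection adds "The research assistant will also meet with participants at subsequent treatment cycles", for the T2 to T6 questionnaires. Only the graduate research assistant who makes the weekly calls is described as blinded.
- **Stratification.** "A stratified sampling strategy followed by randomization will be used". The sentence that follows gives recruitment percentages by sex, race and ethnicity. No stratum is named for the randomization itself.
- **Sites and covariates.** Settings describes a community cancer centre in Orlando and a comprehensive cancer centre in Miami. Data Analysis, Aim 1 lists seven demographic and five experiential covariates. Emetic potential is one of them and site is not. Aim 2 carries the same list into the between-group models.
- **Outcomes.** CINV severity is a self-rated 0 to 10 score. Health care use is reported by the participant and checked against records where that can be done.

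**The concern.** Picking from a set of envelopes differs from opening the next one in a numbered series. In a numbered series, each enrolment has one assignment fixed in advance, and a skipped, repeated or swapped envelope shows as a gap. With a free pick no assignment belongs to any enrolment position, so a second pick would leave no mark in the sequence.

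This matters more than usual here. The role that screens from the medical record and approaches the patient also delivers the intervention at that visit and later helps with the questionnaires. Intervention participants know they have played the game, and the primary outcomes are self-reported. Concealment before assignment is therefore one of the few protections left against selection bias. The planned comparison of groups at baseline and the covariate adjustment deal with measured factors only. They would not reveal or remove selection on something unrecorded, such as how unwell or how motivated a patient appeared.

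Site is a separate and smaller gap. Two different kinds of centre are pooled, and site is in neither the described allocation nor the models.

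**Working it through.** There is no stated figure to reproduce, because the point is about procedure. The calculations below size what is at stake and test whether chance imbalance is a serious part of it.

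**1. Passages side by side.** The mechanism is a choice by the participant. The timing is after baseline measures and before immediate delivery of the game. Screening, approach, delivery and visit data collection all fall to the research assistant role. No independent allocator is described, and no custodian of the envelopes is named.

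**2. Covariate count.** 7 demographic + 5 experiential = 12 covariates. Emetic potential is present and site is absent.

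**3. Chance imbalance in a binary factor such as site.** Inputs: N = 500 (Power Analysis and Sample Size). The share p with the factor is not given, so it is assumed to lie between 0.2 and 0.5. Under unrestricted 1:1 allocation, the SE of the difference in share between arms = √(4p(1−p)/N).

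| p (assumed) | SE | 95% range | P(difference > 10 points) | P(difference > 5 points) |
|---|---|---|---|---|
| 0.2 | 0.036 | ±7.0 points | 0.5% | 16% |
| 0.3 | 0.041 | ±8.0 points | 1.5% | 22% |
| 0.5 | 0.045 | ±8.8 points | 2.5% | 26% |

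Large chance imbalance is unlikely at this sample size.

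**4. Illustration of steering (assumed inputs).** Suppose a fraction f of each arm is exchanged between participants whose expected nausea differs by g points. Each arm mean moves by f × g in opposite directions, so the group difference moves by 2fg.
- f = 5% (12.5 of 250), g = 2: 12.5 × 2 / 250 = 0.1 per arm, 0.2 in total.
- f = 5%, g = 1: 0.1 in total.
- f = 2.5%, g = 1: 0.05 in total.

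The planned difference is 1. Neither f nor g comes from the document.

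**5. What such a shift would do to the test.** Two standard errors can be obtained from the plan's figures:
- one measurement per person: 2.44 × √(2/250) = 0.218;
- implied by 87% power for a difference of 1: 1/(1.96 + 1.13) = 0.324.

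With no true effect, the chance of p < 0.05 (two-sided) is P(Z > 1.96 − b/SE) + P(Z < −1.96 − b/SE), where b is the shift.

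| Shift b (assumed) | SE 0.218 | SE 0.324 |
|---|---|---|
| 0.05 | 5.6% | 5.3% |
| 0.1 | 7.4% | 6.1% |
| 0.2 | 15% | 9.5% |

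These results are conditional on the assumed shift. They are not evidence that any shift occurred.

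**The case against.** The best defence is that an article condenses the full protocol. Sealing, opacity, numbering, envelope preparation and draw logs are details that an article commonly leaves out, and the full protocol is not shown. The text gives the choice to the participant, after baseline measures. If the contents are hidden and the set is mixed, the research assistant has nothing to predict. Unstratified allocation of 500 people is a legitimate design.

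Much of this stands, and it rules out three stronger readings.

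- A reader might infer that enrolling staff hold the envelopes and can steer who goes where. No custodian is named and no steering is shown. It is a risk that the text does not exclude.
- A reader might infer that the arms are unbalanced by site or emetic potential. Randomization balances both in expectation, and a gap above 10 points has a chance of about 0.5% to 2.5% under the assumed shares. Emetic potential is already in every model. Unequal arm sizes hardly matter either. Independent tosses would give about 228 to 272 per arm, with relative efficiency at the extreme of 4 × 228 × 272 / 500² = 0.992. A prepared set with equal numbers per arm would vary less.
- A reader might take the 0.2-point shift as an estimate of bias. It rests entirely on assumed inputs.

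What the defence does not answer is that the free choice is stated, not merely left undescribed. Sealed and opaque envelopes would still not make it a sequence tied to enrolment order. The absence of site from an explicit covariate list is also stated content.

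**Conclusion.** The point holds in a limited form. The plan states an allocation by free choice, which follows no fixed order. It places that choice at the visit where the role that enrols participants also delivers the game. As described, allocation is not shown to be concealed or auditable. Site is missing from the covariates and from any described stratification of the allocation.

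The size of any resulting bias cannot be derived from the document. The shifts of 0.05 to 0.2 points are illustrations under assumed exchange rates and prognostic gaps. The imbalance figures assume unrestricted allocation and a site share between 0.2 and 0.5. The conclusion about concealment rests on the article alone. If the full protocol shows numbered, sealed, opaque envelopes opened in order, what remains is correcting the article's description and adding site. Because the safeguards cost little and cannot be added for participants already allocated, the change should be made for those still to come.

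**What to change.** 1. For all remaining participants, replace the free choice with a concealed, pre-generated sequence stratified by site, for example permuted blocks of varying size. Release each assignment through REDCap only after that participant's baseline data are saved. The minimum alternative is sequentially numbered, sealed, opaque envelopes, prepared by staff not involved in enrolment and opened in order.
2. Add site as a covariate in all Aim 2 models. Emetic potential is already there and needs no change.
3. Run a sensitivity analysis by enrolment before or after the switch.
4. State in the protocol how envelopes were prepared, held and recorded for participants already allocated.

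**Cost.** A short amendment and a small set-up task. Data Management and Integrity describes two separate REDCap systems with the same structure, so each site needs its own list. The article does not mention a randomization module, so its availability is an assumption. The trial would contain two allocation methods, which item 3 addresses. Results reports 130 enrolled by July 2023. On that count 500 − 130 = 370 allocations, or 610 − 130 = 480 on the larger enrolment target, were still to come. The present number is unknown and will be smaller if enrolment has continued.

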### Intervention

The intervention consists of three parts: (1) the MAH serious game, (2) self-care discussion with the research assistant, and (3) follow-up.

#### Part 1: The MAH Serious Game

The game will be administered and supervised by the research assistant. Participants will play the game on an iPad at the outpatient treatment center prior to their first chemotherapy treatment. Headphones can be used to ensure privacy and limit distraction. During the game, players make decisions for the avatar based on common CINV management practices (eg, taking medication, dietary strategies, and staying hydrated; Textbox 1), which cause the avatar to become nauseated or be nausea-free.

#### Part 2: Self-Care Discussion With the Research Assistant

At the end of the game, the research assistant will answer any questions the participant has and make clarification when needed. In the event, if a participant’s avatar has a negative outcome (ie, severe nausea), self-management behaviors will be corrected by the research assistant. In our pilot study, these discussions varied between none and 1 or 2 questions from participants. Based on our pilot data, we estimate that 10% (n=25) of players needed a more in-depth discussion to correct self-management behaviors. In this study, we will document the types of questions asked and the content of these discussions to improve the internal validity of the intervention. We will also document the involvement of caregivers in the intervention, if it occurs.

#### Part 3: Follow-Up

Participants will be allowed to play the game as many times as they choose during that chemotherapy visit or at subsequent visits in order to practice making decisions and visualizing consequences and outcomes. Once the participant is discharged home, the graduate research assistant (GRA), blinded to the treatment group, will call participants weekly to see how they are doing and remind them to respond to data collection texts or use paper or pencil forms. To reduce bias, a scripted interview form will be used, and no “teaching” will occur. Calls will only be to check in with the participants and remind them to collect data. If participants ask questions about managing CINV and other symptoms, the GRA will instruct them to contact their oncology team for additional management. In addition, participants will be asked to follow cancer center procedures and call their oncologist if they are having problems or have questions.

### Treatment Fidelity and Monitoring

The MAH will be presented and delivered by research assistants who have been trained in the game and CINV symptom management strategies. The research assistant will answer questions during the decision discussion based on common self-management options (Textbox 1). A checklist for each interaction with the participant will guide each encounter. Minor interruptions (<10 minutes) to gameplay will be recorded, and participants will resume gameplay where they left off. Technology malfunctions (eg, frozen screen) will be recorded, and participants will be asked to start MAH over again using a new iPad.

### End Points

The study will continue until one of the following end points is met: (1) completion of the study, (2) no longer receiving chemotherapy treatment, or (3) unreasonable delays in treatment.

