## Introduction

### Background

Older adults (≥65 years) represent about 15% (46 million) of the US population, and the rate is expected to double (90 million) by 2050 [1-3]. They also represent 55% of all cancer diagnoses [2,4]. With an aging population, the number of older adults with cancer will also increase, taxing limited health care resources. Despite advances in antiemetic therapy, older adults diagnosed with cancer experience chemotherapy-induced nausea and vomiting (CINV) [5]. Although older adults are less likely to have CINV symptoms, they are more likely to experience serious consequences (eg, dehydration and renal impairment) than younger adults [6-8] due to the presence of multiple comorbidities, compromised organ function, frailty, and decreased overall functioning [9-11]. CINV occurs in up to 80% of adults receiving chemotherapy [12,13] and can lead to metabolic and nutritional issues (eg, loss of appetite, weight loss, and malnutrition), decrease in self-care and functioning, decline in physical and mental status, and poor quality of life (QOL) [12]. Up to 47% of adults receiving moderate to high emetogenic chemotherapy will experience a hospital admission (HA) related to CINV [14,15] and ~20% will have an unplanned emergency department (ED) visit [16]. The Centers for Medicare and Medicaid Services [17] urge improving care and reducing unplanned ED visits in those receiving cancer treatment. Therefore, interventions are needed to decrease CINV symptoms, improve functioning and QOL among older adults, and reduce health care use due to poor CINV symptom self-management.

Despite clinical guidelines for managing CINV, ~49% of adults with cancer are undertreated for CINV [13,18], and prevention of CINV remains a challenge [5]. Risk factors for undertreatment include the type of chemotherapy, being treated in the outpatient clinic, and out-of-pocket costs for antiemetics [18]. Health care practitioners report that managing breakthrough nausea within the first 5 days after chemotherapy is a common occurrence, while managing delayed CINV is the most challenging [19]. About 32% of practitioners report the need to stop or delay cancer treatment in patients due to CINV [19].

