### Power Analysis and Sample Size

For aim 1, when the outcome of interest is continuous (eg, CINV severity and number of self-management behaviors), a sample of 100 participants, measured continuously throughout the study period between T1 and T6, achieves a power of 0.904 when using a chi-square test from a generalized estimating equation (GEE) analysis to test whether the average slope of the participants differs significantly at a significance level of .05. The residual SD is anticipated to be 1.00. Missing values are assumed to occur completely at random (missing completely at random [MCAR]). These missing value proportions will be combined to form the pairwise observant probabilities using the independent method. The anticipated proportions missing at each measurement time are 0.00, 0.08, 0.16, 0.24, 0.32, and 0.40. The first row of the autocorrelation matrix of the responses within a participant is assumed to be 1.0000, 0.4000, 0.1600, 0.0640, 0.0256, and 0.0102. Other rows follow the same pattern. For aim 1, a total of 254 participants, each scheduled to be measured 6 times, achieves a power of 0.90 when using a 2-sided Wald test from a GEE analysis with a count outcome (eg, QOL) to test whether a μ1(1) of 0.500 differs from a μ2(1) of 1.000 at a significance level of .05. μ1(0) and μ2(0) are assumed to be 1.000. Missing values are assumed to occur completely at random (MCAR). These missing value proportions will be combined to form the pairwise observant probabilities using the independent method. The anticipated proportions missing at each measurement time are 0.00, 0.08, 0.16, 0.24, 0.32, and 0.40. The first row of the autocorrelation matrix of the responses within a participant is assumed to be 1.000, 0.500, 0.250, 0.125, 0.063, and 0.031. Other rows follow the same pattern.

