For aim 1, when the outcome of interest in binomial (eg, resource use), a sample of 357 participants, each scheduled to be measured 6 times, achieves a power of 0.90 when using a 2-sided Wald test from a GEE analysis with the binary outcome to test whether a P1(1) of 0.500 differs from a P2(1) of 0.250 at a significance level of .05. P1(0) and P2(0) are assumed to be 0.500. Missing value (MCARs) proportions will be combined to form the pairwise observant probabilities using the independent method. The anticipated proportions missing at each measurement time are 0.00, 0.08, 0.16, 0.24, 0.32, and 0.40. The first row of the autocorrelation matrix of the responses within a participant is assumed to be 1.000, 0.500, 0.250, 0.125, 0.063, and 0.031. Other rows follow the same pattern.

For aim 2, based on the assumption of a nausea severity mean score of 6.20, range from 2 to 9, an SD of 2.44, and a clinically meaningful difference in mean nausea severity score of 1 between the IG and control group, a sample size of 500 participants (250 per group), measured between 6 and up to 30 times (depending on the outcome variable of interest), achieves 87% power to detect a difference between the (fixed) group means. The ratio of the subject-specific slope variance to σ² is 0.100. The correlation between measurements within a participant is 0.100. The test was based on a mixed model regression analysis using a significance level of .05. This power analysis was calculated using PASS 20 (NCSS LLC). Anticipating an attrition rate of ~22%, we will seek to enroll 610 older adults for this study. Attrition to mortality is not expected to be high due to the exclusion criteria for those with less than 6 months to live.

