### Outcome Measures

#### Primary Outcome Measures

##### Health Care Resource Use

Health care resource use is defined as any unplanned ED admission or HA and will be recorded via participant report using a dichotomous(Y/N) variable at each follow-up phone contact, text, and treatment visit. Follow-up questions about the reason for the admission, length of time for admission, and treatment will also be asked. The report will be verified by medical record review whenever possible.

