Changes in primary and secondary outcomes from T1 to T6 will be assessed using linear (CINV severity, self-management behaviors, cognitive representation, and functioning), binary (resource use), and ordinal (QOL) regressions, as appropriate, within a GEE framework. All models will control for the effects of 7 demographic (age, gender, race or ethnicity, comorbidity, education level, income level, and insurance status) and 5 experiential (cancer type, emetic potential, treatment frequency, intake of IV fluids between treatment cycles, and number of home antiemetics) variables. GEE models are well suited for this type of repeated measures design, as they account for within-subject correlations between repeated measurements over time in a longitudinal design. Furthermore, GEE models are not restricted by any distributional assumptions including the assumptions of normality required by most other approaches to longitudinal analysis such as repeated measures ANOVA. Finally, GEE models provide robust parameter and SE estimates even if the working correlation structure for the data is misspaced [61]. The analysis will be 2-tailed and conducted with SAS (version 9.4; SAS Institute Inc).

#### Aim 2

Aim 2 determines the efficacy of the MAH intervention by comparing differences in primary outcomes (CINV severity and health care use) and secondary outcomes (self-management behaviors, functioning, and QOL) between the IG and control group at each follow-up visit (T_2_-T_6_) and completion of the study (T_6_). We hypothesize that the IG will report lower levels of CINV severity and health care use at T_2_-T_6_ than the control group. We hypothesize that the IG will report higher levels of self-management behaviors, functioning, and QOL at T_2_-T_6_ than the control group.

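### Follow-up ends when chemotherapy stops or is unreasonably delayed, which CINV can cause; this conflicts with the MCAR assumption and GEE of Aim 1 and leaves later ED visits and admissions uncollected

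*Protocol article*

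**What the plan says.** All references are to the protocol article.

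- **End Points.** The study continues until "completion of the study, (2) no longer receiving chemotherapy treatment, or (3) unreasonable delays in treatment". The second and third conditions can only be met by an individual, so this reads as the rule that ends each participant's follow-up.
- **Introduction, Background.** "About 32% of practitioners report the need to stop or delay cancer treatment in patients due to CINV".
- **Aims and Hypotheses.** CINV severity and health care use are the primary outcomes. The intervention is meant to lower both. Aim 1 expects them to fall within the intervention group from T1 to T6.
- **Power Analysis and Sample Size.** For the continuous and count outcomes of Aim 1, "Missing values are assumed to occur completely at random". For the binary outcome, "Missing value (MCARs) proportions will be combined to form the pairwise observant probabilities using the independent method". In all three calculations the missing proportions at T1 to T6 are 0, 8, 16, 24, 32 and 40%. For Aim 2 the section gives about 22% attrition and no missingness mechanism.
- **Data Analysis, Aim 1.** Outcomes are modelled by linear, "binary (resource use), and ordinal (QOL) regressions, as appropriate, within a GEE framework", adjusted for 12 demographic and experiential variables. No weighting for dropout is described.
- **Data Analysis, Aim 2.** Group differences at each visit and at T6 are assessed with generalized linear mixed models (GLMMs).
- **Health Care Resource Use.** Any unplanned ED visit or admission is asked about at every phone contact, text and treatment visit. "The report will be verified by medical record review whenever possible".
- **Experiential Characteristics.** Treatment delays, dose reductions and chemotherapy changes are taken from the medical record.

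**The concern.** MCAR requires that the chance of a missing visit has nothing to do with the participant's outcomes. The End Points rule removes participants for events that, by the Background's own account, severe CINV can bring about. If those with worse nausea leave sooner, the participants seen at T5 and T6 are selected for tolerating treatment.

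Two things are at stake. First, the Aim 1 trend has no comparison group to cancel this selection, and the selection pushes it in the hypothesised direction. Second, an ED visit or admission is just as well defined after chemotherapy stops as before. Ending follow-up there discards part of a primary outcome, possibly in the participants most likely to have such events.

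**Working it through.** **1. The plan's own Aim 1 figures rest on MCAR.** Inputs from Power Analysis and Sample Size: six visits; observed proportions 1.00, 0.92, 0.84, 0.76, 0.68, 0.60; AR(1) correlation 0.5; probabilities 0.50 rising or falling to 0.50 versus 0.25; two-sided 0.05; power 0.90. The method assumes a linear trend on the link scale over time 0 to 1, working independence, and joint observation probabilities equal to the product of the marginal ones, which is the independent MCAR case.

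Per-participant sandwich variance of the slope: V = [A⁻¹BA⁻¹] for the slope term. A weights each visit by its observed proportion, and B weights each pair of visits by its joint observation probability.

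- Binary: V₁ = 9.539, V₂ = 10.909, slope difference = ln(0.25/0.75) = −1.0986. N = 2 × (1.960 + 1.282)² × (9.539 + 10.909) / 1.0986² = 356.03, rounded up to **357**, as stated.
- Count (means 1.0 versus 0.5): V₁ = 2.385, V₂ = 3.421, difference = ln 0.5 = −0.6931. N = 2 × (1.960 + 1.282)² × 5.806 / 0.6931² = 253.9, rounded up to **254**, as stated.

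So both figures reproduce under independent MCAR. With the same proportions, 250 × 0.60 = 150 per arm would be seen at T6.

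**2. What severity-related leaving does.** The documents do not say how strongly leaving depends on nausea, so a range was simulated.

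- From the plan: mean 6.20, SD 2.44, six visits, 40% missing at T6 (applied to the intervention group in the no-change runs and to the control arm in the two-arm runs), and a between-group difference of 1 point.
- Assumed: once a participant leaves, all later visits are missing. The log-odds of leaving rise by 0.5 or 1.0 per SD of nausea, either at the previous recorded visit (MAR) or at the current unrecorded one (MNAR). Correlation is AR(1) 0.4 or 0.5, or exchangeable 0.1 or 0.4. There are 200,000 simulated participants per arm.

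The AR(1) values and the exchangeable 0.1 come from the power section; exchangeable 0.4 is an added assumption. The false fall is minus five times the working-independence GEE slope per visit when the true change in the intervention group is zero. The T6 difference is among those still observed when the true difference is 1.00.

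| Correlation | Log-odds per SD | False fall, MAR | False fall, MNAR | T6 difference, MAR | T6 difference, MNAR |
|---|---|---|---|---|---|
| AR(1) 0.4 | 0.5 | 0.06 | 0.19 | 0.98 | 0.99 |
| AR(1) 0.4 | 1.0 | 0.15 | 0.33 | 0.97 | 0.91 |
| AR(1) 0.5 | 0.5 | 0.11 | 0.22 | 0.97 | 0.97 |
| AR(1) 0.5 | 1.0 | 0.19 | 0.40 | 0.96 | 0.90 |
| Exch. 0.1 | 0.5 | 0.05 | 0.13 | 1.00 | 0.97 |
| Exch. 0.1 | 1.0 | 0.11 | 0.27 | 0.98 | 0.91 |
| Exch. 0.4 | 0.5 | 0.23 | 0.29 | 0.96 | 0.96 |
| Exch. 0.4 | 1.0 | 0.41 | 0.50 | 0.91 | 0.88 |

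- **Within the intervention group**, maximum likelihood on the same data gives a change of about zero under MAR and a false fall of 0.14 to 0.33 under MNAR.
- **Between groups**, maximum likelihood gives 0.99 to 1.01 under MAR and 0.92 to 0.99 under MNAR. Missingness at T6 becomes unequal: about 40% in the control arm against 30 to 36% in the intervention arm.

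**3. Health care use.** No size can be computed, because the documents give no event rate after chemotherapy stops. The point follows from the text alone: the outcome is any unplanned ED visit or admission, and collection ends with the participant's follow-up.

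**The case against.** Much of the case on the other side stands.

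- **A reader might infer that the efficacy comparison depends on MCAR.** The documents do not support that. MCAR is stated only for the Aim 1 power. Aim 2 uses a GLMM which, if fitted by likelihood, needs only MAR and uses every randomised participant's observed data. The bias left in nausea is modest and toward no effect.
- **A reader might put the error near a full point.** If all 40% missing at T6 were leavers with nausea 2 points worse, the observed mean would be 0.40 × 2 = 0.8 too low; 40% against 30% leaving would give 0.10 × 2 = 0.2 between arms. Neither figure is supported. The 40% covers missingness from any cause, the 2-point gap and the 30% are not in the documents, and the 1-point target is a between-group difference that a within-group shift cannot be set against. The 32% in the Background is a share of practitioners, not of patients.
- **The rule is not purely a CINV rule.** It covers stopping chemotherapy for any reason, including planned completion, and only delays judged unreasonable.
- **GEE tolerates some dropout.** Dropout explained by the baseline covariates in the model does no harm. Only the remaining dependence on outcomes matters, and its strength is unknown.
- **Missing-data handling may be set out in an analysis plan not shown.** That is fair, and silence is not the complaint. The stopping rule and the MCAR assumption are both stated and do not agree, and no later plan can restore events that were never collected.
- **CINV has no clear meaning off chemotherapy.** Agreed: an on-treatment window is a defensible choice for that outcome.

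**Conclusion.** The point holds for Aim 1 and for health care use. The End Points rule makes dropout that depends on CINV likely, while the Aim 1 power assumes there is none and the Aim 1 GEE makes no stated allowance for it. With no true change, the intervention group could appear to improve by 0.05 to 0.41 points (MAR) or 0.13 to 0.50 (MNAR). The upper ends need the exchangeable 0.4 correlation; under the plan's own correlations the ranges are 0.05 to 0.19 and 0.13 to 0.40. All of these rest on the assumed dropout strengths.

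For nausea in Aim 2, the effect is a modest loss of the true difference, not false efficacy. For ED visits and admissions, the loss after chemotherapy stops affects Aim 2 as well, has unknown size and direction, and cannot be repaired in analysis.

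**What to change.** 1. **Separate the end of chemotherapy from the end of data collection.** For every randomised participant, continue to record ED visits and admissions to the cycle-6 or 6-month date through the existing weekly calls and record review, and analyse them as randomised. This leaves clinical management unchanged.
2. **Keep CINV severity as an on-chemotherapy measure**, say so, and report stopping and delay by arm from the treatment-change data already collected.
3. **For Aim 1, replace plain GEE** with a likelihood-based mixed model or dropout-weighted GEE. Either removes the bias from leaving that follows recorded severity, provided the model is right; neither removes the part that follows unrecorded severity. State that the Aim 1 power figures hold only under MCAR.

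The cost is extra calls and record review for participants who stop, plus protocol wording. With 130 enrolled by July 2023 and data collection and analysis due to be complete in 2027, an early change would still reach many participants. QOL after stopping is optional: it is completed on an iPad at treatment visits, so it would need a new collection route.
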